#### Additional analysis

The COVID-19 pandemic occurred while the recruitment was still ongoing. A growing literature has shown the impact of restrictive measures adopted during the pandemic such as isolation and COVID-19 infection on cognitive decline [46–48]. Data regarding COVID-19 infections, severity of COVID-19 leading to hospitalisation and requirement of intensive care unit and vaccination status will be reported. Characteristics of individuals enrolled before and during the pandemic period will be compared to verify whether the pandemic had an impact on the recruitment of participants. Furthermore, the association of COVID-19 infection will be evaluated by univariate and multivariable Cox model including the status variable as time-dependent.

#### Analysis of secondary clinical endpoints

For secondary clinical endpoints, conversion to AD in amnesic patients and conversion to other forms of dementia, univariate analysis will be repeated. The final multivariable predictive model identified in the primary analysis will be applied. The model performance will be assessed by Harrel’s C-index, as well as the other performance measures specified in the primary analysis.

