#### Secondary outcome

The secondary outcomes are the conversion to Alzheimer’s disease within 3 years of follow-up in amnesic patients and the conversion to other forms of dementia.

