For CSF biomarkers, the following fluid levels are considered: threonine-181 (p-tau), total-tau (t-tau), amyloid-beta Aβ1-42, Aβ_1-42/1–40_ ratio, Aβ_1-42_/p-tau ratio. ^18^Fluorodeoxyglucose positron emission tomography (^18^F)FDG-PET is analysed with voxel-based single subject using the optimised procedure based on statistical parametrical mapping (SPM), involving a large database of normal controls for comparison and the new FDG atlas for normalisation [10, 11]. Two techniques are used to compute the right and left hippocampal volumes, normalised to the intracranial volume in volumetric MRI. The first technique is ACM-Adaboost, which is a machine learning algorithm used to classify the voxels belonging to the hippocampal region. The second technique is Freesurfer v6.0, which is a surface-based approach [12]. Seven parameters of Small World (SW) are computed in delta, theta, alpha1, alpha2, beta1, beta2 and gamma frequency bands to evaluate the brain connectivity via graph theory in EEG [13]. As part of the study, each participant is required to undergo all necessary tests for biomarker acquisition. These tests are required to be completed within 60 days from the neuropsychological battery assessment and the acquisition of informed consent at the beginning of the study. Biomarker testing is conducted in a blinded manner, meaning that the data collected at baseline, including predictor variables such as biomarkers and any information related to medical history or clinical examination, are not taken into account during biomarker testing. Moreover, to improve the predictive accuracy of biomarkers, clinical and demographic characteristics will be also considered. A critical review of the relevant literature was conducted to identify factors associated with the development of dementia [14, 15]. The following predictors, selected according to the clinical relevance among all the demographic and clinical variables collected, will be used in the development and validation of the multivariable prediction model: sex, age, level of education (measured in years of education), type of MCI (amnesic, non-amnesic) according to single or multiple domains, Amsterdam IADL (short version) [16], Cumulative Illness Rating Scale (CIRS) including severity and comorbidity index [17], hypertension, family history of dementia, smoking status, status of cohabitation as a proxy of social isolation, psychiatric disease (past and present) and cardiovascular disease. All these data, collected during the clinical assessment visit, could significantly improve the accuracy of the prediction model. All predictors are collected at baseline.

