#### Predictive performance

For each biomarker in the categorical form, the accuracy measures (sensitivity, specificity, positive predictive value, negative predictive value, overall accuracy, positive and negative likelihood ratios) will be calculated for comparison with the literature. For continuous biomarkers, the area under the receiver operating characteristic curve (AUC) will be also reported. Moreover, a univariate analysis will be conducted using the proportional hazard Cox model.

To evaluate the performance of the prediction models, several measures will be considered. The concordance c-index with its 95% CI will be provided as a discrimination measure and the extensions of binary AUC to survival analysis proposed by Harrell will be used [40, 41]. The Akaike information criterion will be provided as a measure of the goodness of fit of the model.

The added value on performance of each biomarker to the multivariable model with demographical and clinical variables will be assessed by the category-free Net Reclassification Improvement (NRI), which is the net proportion of events reclassified correctly plus the net proportion of non-events reclassified correctly. The delta AUC (difference in c-statistics) will be also provided [41], and the likelihood ratio test will be used to assess the statistical significance of the incremental contribution of each biomarker [36, 37].

In addition, to assess the predictive performance of the final multivariable model, calibration measures will also be reported [38, 42]. A calibration plot will be done by plotting the observed outcome proportion (on the *y*-axis) versus the ordered predicted outcome probabilities (on the *y*-axis) by quantile of the predicted risk. Subsequently, the calibration intercept and slope and their 95% CI will be estimated. There is a perfect calibration when the intercept is zero and the slope is one. Moreover, overall measures of performance, the Nagelkerke’s *R*^2^ and the Brier score, will be provided. The Brier score is a composite measure of discrimination and calibration with lower scores indicating improved model accuracy, and it will be calculated at a fixed time point (3 years).

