#### Internal validation

The final predictive model will be internally validated using the bootstrap technique with 500 bootstrap samples [38]. The stepwise selection will be repeated in the validation process (i.e. stepwise procedure will be repeated within each bootstrap sample). Consequently, Harrel’s c-index of the predictive model will be adjusted to take into account the estimated potential overfitting and a corrected c-index will be reported. Apparent and corrected calibration measures will be reported [44]. The correction will be performed using the shrinkage factor calculated with bootstrapping. The shrinkage factor may take values between 0 and 1, and a value above 0.90 indicates a small overfitting. As the shrinkage of regression coefficients is an important way to reduce overfitting, the shrinkage factor will be also applied to regression coefficients and intercept of the final model [38] to improve the prediction ability of the regression model when applied to external data. Both the original and shrunken regression coefficients will be reported.

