### Model presentation and risk groups

For each predictive model, the hazard ratios with 95%CI and *p*-value will be reported. For the final predictive model, a nomogram will be generated. A nomogram is a graphical representation of the statistical predictive model. It is a visual tool that translates model numeric results into a visual format, making it easier to estimate an outcome based on multiple variables. Each variable occurrence is assigned a specific score based on its contribution to the overall prediction. The total score from all variables is then used to estimate the probability of the predicted event (in this case, the conversion to AD at 3 years) conditioning to the individual characteristics [45]. For this purpose, the covariates in the Cox model will be centred. Sensitivity and specificity corresponding to different thresholds of the prediction risk score will also be provided for the final model. Finally, three or more risk categories will be proposed defining low-, medium- and high-risk groups based on the predictive risk score considering the highest sensitivity corresponding to an adequate level of specificity. This category definition will help the clinician with the choice to treat individuals with MCI based on the likelihood of converting to dementia in the following 3 years. Because avoiding the clinical consequence of treating a false positive is a target as important as treating a true positive, a rate of false positives less than 20% (i.e. specificity of at least 80%) is considered acceptable for a medium–high-risk group. We will start by inspecting deciles of the predictive score and grouping them into homogeneous classes based on levels of sensitivity and specificity. Kaplan–Meier curves will be presented for each risk group.

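### The AD model is also scored against conversion to other dementias, where calibration and Brier score are uninterpretable if coefficients are fixed and poorly supported if they are refitted

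*SAP article*

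**What the plan says.** The *Secondary outcome* section names two endpoints: AD conversion "in amnesic patients and the conversion to other forms of dementia". In *Analysis of secondary clinical endpoints* the univariate analyses are repeated for each, and then: "The final multivariable predictive model identified in the primary analysis will be applied". Performance is judged by the C-index, "as well as the other performance measures specified in the primary analysis".

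Those measures are listed in *Predictive performance*. Besides discrimination they include calibration ("the calibration intercept and slope and their 95% CI will be estimated") and a Brier score at 3 years. The event the model predicts is named in *Model presentation and risk groups*: "in this case, the conversion to AD at 3 years".

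Optimism is handled in *Internal validation*: "The final predictive model will be internally validated using the bootstrap technique with 500 bootstrap samples". The secondary-endpoint section does not mention that correction. *Sensitivity analysis* names death as a competing event and no other.

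**The concern.** A model whose predictors, coefficients and baseline hazard are chosen for AD is to be scored on a different outcome. Calibration and the Brier score are meaningful only when the predicted and observed events are the same. The key word, applied, has two readings: carry the fitted AD model over unchanged, or refit its predictors to each endpoint. The plan does not choose between them, and for other dementias each has a problem.

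At stake is how a named secondary outcome will be read. Under fixed coefficients, poor calibration would look like model failure when it only reflects the change of event. Under a refit, an apparent C from few events could look like real predictive ability.

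A smaller matter concerns the amnesic endpoint. Those patients belong to the cohort on which the model is developed, and the text does not say whether their performance figures will be apparent or optimism-corrected.

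**Working it through.** **1. The plan's own figures.** The nearest stated figure is the *Sample size* section's 9.5 events per parameter and up to 17 candidate predictors. It reproduces with the Riley shrinkage criterion at S = 0.90 and R² = 0.31:

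- Subjects per parameter: 1/[(0.90 − 1) × ln(1 − 0.31/0.90)] = 23.68.
- Events per parameter: 23.68 × 0.16 × 2.5 = 9.47 (stated 9.5).
- Subjects for 17 parameters: 17 × 23.68 = 402.6, in line with 400 evaluable.

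This calculation is for AD. No figure is given for other dementias.

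**2. Fixed coefficients.** Inputs are an AD incidence of 27% to 40% (the Table 2 range), taken as the mean predicted risk of a model well calibrated for AD, and a non-AD dementia incidence of 5% to 10%. The second is an assumption, because the article gives no value. Observed/expected = non-AD incidence / mean predicted AD risk:

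| Non-AD incidence (assumed) | AD risk 40% | AD risk 27% |
|---|---|---|
| 5% | 0.05/0.40 = 0.125 | 0.05/0.27 = 0.19 |
| 10% | 0.10/0.40 = 0.25 | 0.10/0.27 = 0.37 |

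The range is about 0.13 to 0.37. The shortfall arises from the change of event and says nothing about the quality of the model.

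**3. Same predictors refitted.** Mean predicted risk now follows the non-AD incidence, so the ratio in step 2 no longer applies. The events are few:

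- Other dementias at N = 400: 400 × 0.05 = 20 to 400 × 0.10 = 40.
- AD at 40%: 400 × 0.40 = 160.
- Carrying over the plan's 9.5 events per parameter as a rough guide only: 20/9.5 = 2.1 to 40/9.5 = 4.2 parameters. Age and sex, which are forced in, already use two.

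The *Discussion* says that recruitment fell short of 500, so the counts would be lower if fewer than 400 are evaluable.

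**4. Illustrative simulation.** Everything in it is assumed: cause-specific Cox models, N of 350 or 400, 17 or 31 candidate parameters, 70% amnesic, backward elimination at p > 0.10, 40 replicates, and 4,000 new subjects for testing. AD incidence was about 42% and non-AD about 8–9%. The four scenarios that completed had non-AD risk factors either unrelated or opposite to those for AD. None with risk factors shared in the same direction completed.

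| Quantity | Development data | New subjects |
|---|---|---|
| AD score on non-AD dementia, C | 0.49–0.51 (unrelated); 0.41 (opposite) | not evaluated |
| AD score on non-AD dementia, observed/expected | 0.18–0.21 | not evaluated |
| Same predictors refitted to non-AD dementia, C | 0.64–0.67 | 0.52–0.57 |
| AD in amnesic subset, C | 0.75–0.76 | 0.72–0.74 |
| AD in whole cohort, C | 0.76–0.77 | 0.74–0.75 |

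The refit gains about 0.10 or more in apparent C that is not there in new subjects. In the amnesic subset the within-scenario gap is about 0.02 to 0.04, similar to the whole cohort.

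**5. Amnesic subset, reading the text.** The outcome is the same as in the primary analysis. One candidate predictor is "type of MCI (amnesic, non-amnesic) according to single or multiple domains". Its amnesic/non-amnesic contrast is constant in this subset, so a somewhat lower C there is expected and is not in itself a sign of poor performance.

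**The case against.** The strongest reply is that the failure of calibration holds only under fixed coefficients, which the article never states. The final model is described as identified through selection, so applying it could mean refitting the selected predictors. That would sit naturally beside the instruction for "conversion to AD in amnesic patients and conversion to other forms of dementia, univariate analysis will be repeated". This stands: the ratio in step 2 is conditional on the fixed reading. It does not remove the point, because the refit has the separate weaknesses in step 3.

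A reader might infer that neither secondary outcome gets a usable answer. The documents do not support that. Univariate analyses are planned for both endpoints, and the C-index of an AD score on non-AD dementia is a legitimate check of whether the score is specific to AD, if it is labelled so.

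A reader might also infer that the amnesic analysis is misleading, or that the bootstrap correction is confined to the whole cohort. Neither follows. The plan does not call the subset analysis validation, and the *Discussion* names the absence of external validation as a major limitation. The reference to the other primary measures can be read to include the corrected ones. What remains is that the correction is not explicit for this subset.

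**Conclusion.** The point holds for other dementias under either reading of the text. With fixed coefficients, calibration and Brier score cannot be read as performance, with observed/expected of about 0.13 to 0.37. With a refit, AD-selected predictors meet roughly 20 to 40 events, without a stated optimism correction and without AD named as a competing event. These sizes rest on an assumed non-AD incidence of 5–10%. The mismatch of events under fixed coefficients does not depend on that figure.

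For the amnesic subset the conclusion is limited to a clarification. The expected optimism is modest, about 0.02 to 0.04 in C under assumed inputs, and the analysis is sound in itself.

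The point is minor: it touches neither the primary model nor the nomogram, but it changes what is reported for a named secondary outcome.

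**What to change.** In *Analysis of secondary clinical endpoints*:

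- State whether the coefficients are fixed (and if so, original or shrunken) or refitted.
- For other dementias, choose one of two routes in advance. Either fit a small cause-specific Cox model with AD and death as competing events and the number of predictors limited by the number of events, or report the univariate results and the C-index of the AD score, labelled as a specificity check, without calibration or Brier score.
- For AD in amnesic patients, report optimism-corrected measures computed in the same 500 bootstrap samples, and note that these patients are part of the development cohort.

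The cost is SAP wording and modest extra code. No new data are needed.

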## Discussion

To our knowledge, the INTERCEPTOR study represents the first publicly funded study to evaluate, through a harmonisation process among specialised centres distributed throughout the Italian territory, a wide set of biomarkers aimed at predicting the conversion from MCI to AD based over an adequate period of follow-up. The strength of this study lies in the inclusion of a broad range of biomarkers and the standardised and homogeneous collection of these biomarkers. Substantial efforts have been made to standardise biomarker acquisition and analysis, with specialised centres providing expertise in risk diagnosis classification [8]. The study has encountered challenges posed by the COVID-19 pandemic, primarily evident in the recruitment slowdown. The COVID-19 pandemic occurred when the study was in the recruitment phase. For patient recruitment, participants needed to undergo multiple visits for clinical assessment and biomarker acquisition, including at clinical centres distinct from the recruitment centre. The pandemic limited access to certain services necessary for clinical visits and biomarker acquisition. The timeline for scheduled visits has been impacted, leading to deviations from the protocol, which will be documented and appropriately addressed. Despite implementing mitigation actions aimed at ensuring the completion of the INTERCEPTOR study, such as extending the recruitment period and introducing remote visits, we were not able to reach the targeted sample size. Although the initial goal of enrolling 500 individuals with MCI was not met, the final sample size is anticipated to provide estimates of accuracy measures with sufficient precision and to enable the development of a predictive model incorporating demographical and clinical information alongside biomarkers. The model will undergo internal validation, enhancing its reliability. Nevertheless, one major limitation of this study is the lack of external validation, which is crucial to assess the generalizability and robustness of the model. However, once the model is defined, a comparison will be made with existing prognostic models for conversion from MCI to AD available in the literature, and the feasibility of conducting an external validation using data provided by other studies will be evaluated. Furthermore, it is important to note that certain methodological decisions, such as handling non-linearity and categorisation of biomarkers, were not strictly guided by the best evidence but were made to prioritise the clinical interpretability and applicability of the model. This highlights a trade-off between model performance and practical utility in clinical settings. The decision to represent the identified predictive model in the form of a nomogram aims to facilitate its interpretability and applicability with the final goal of assisting clinicians in assessing eligibility for prescribing upcoming new treatments proposed for dementia.

## Conclusion

This paper presents the details of the statistical analysis to be conducted in accordance with the relevant guidelines. The results of the pre-specified analyses will be subsequently made available to minimise the outcome reporting bias.

## Data Availability

Not applicable.

## Abbreviations

AD: Alzheimer’s disease
AIFA: Italian Medicine Agency
AUC: Area under the receiver operating characteristic curve
APOE: Apolipoprotein E
CDCD: Center for Cognitive Disorders and Dementia
CDR: Clinical Dementia Rating
CI: Confidence interval
CSF: Cerebrospinal fluid
DFR: Delayed free recall
DSM-5: Diagnostic and Statistical Manual of Mental Disorders, Fifth Edition
EEG: Electroencephalogram
EMA: European Medicines Agency
FCRST: Free and Cued Selective Reminding Test
FDA: Food and Drug Administration
FDG-PET: Fluorodeoxyglucose-positron emission tomography
MCI: Mild cognitive impairment
MMSE: Mini-mental state examination
MRI: Magnetic resonance imaging
ML: Machine learning
NIA-AA: National Institute on Aging-Alzheimer’s Association
NRI: Net Reclassification Improvement
ROC: Receiver operating characteristic
SPM: Statistical Parametrical Mapping
SW: Small World
TRIPOD: Transparent Reporting of a multivariable prediction model for Individual Prognosis Or Diagnosis
VIF: Variance inflation factor
